#### Secondary outcomes

The secondary outcomes include the cumulative percentage of incident myopia, the cumulative percentage of fast myopic shift of SE, and the change in mean axial length between the baseline visit and subsequent 3-month visits over the study period in each group.

#### Exploratory outcome

Lifestyle/behavior, such as near work time and outdoor time, are potential confounding factors for myopia development. Eye care instruction may impact near work time and outdoor time. We will evaluate the changes in these factors over the study period and include them as the exploratory outcomes. Besides, time to myopia onset and changes in mean subfoveal choroidal thickness over the study period will also be exploratory outcomes.

#### Definition of outcome

According to recent large-scale epidemiological studies on childhood myopia and the definition proposed by the International Myopia Institute [5,6], myopia is defined as SE ≤−0.5 D and high myopia as SE ≤−6.0 D when ocular accommodation is relaxed. Subjects with SE ≤−0.5 D in either eye are classified as having myopia and those with SE ≤−6.0 D in either eye as having high myopia. A fast myopic shift of SE is defined as the myopic shift of SE ≥0.75 D over the first nine months and ≥1.50 D over 18 months. To avoid binocular interaction bias, only the eye with less SE at baseline (less positive or more negative refractive error) in each child was included to analyze study outcomes related to SE and axial length changes.

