#### Primary outcome

The primary outcome is the change in mean cycloplegic SE between the baseline visit and subsequent 3-month visits over the study period in each group.

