### Eye examinations

At baseline visit and subsequent 3-month follow-up visits over the study period, all participants will receive the eye examination, including assessments of uncorrected/corrected visual acuity, external eye, ocular alignment, extraocular muscle motility, axial length measurement, choroidal thickness measurement, refractive status before and after cycloplegia, and a dilated fundus examination.

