### Statistical analysis

The database of examination parameters and questionnaire items of this study will be constructed with Microsoft Excel software (Redmond, WA, USA). Only the data from the eye with less SE (more myopic or less hyperopic) in each child will be used for identifying refractive status and ocular parameter analysis. Continuous variables will be expressed as mean (SD). Categorical variables will be expressed as frequency and percentage. The independent Student’s t-test, ANOVA, or Pearson’s chi-square test will be adopted to compare the differences between groups in terms of refractive error, demographic characteristics, and questionnaire items. Repeated measures ANOVAs will be used to test the interaction effect of time and treatment for the repeated measures during the follow-up examinations. Statistical analysis will be carried out using IBM SPSS Statistics 26 (IBM Corp., Armonk, N.Y., USA). All p values < 0.05 are considered statistically significant.

For the analysis of the primary outcome, the 1.5-year myopic shift of SE is calculated as the difference in SE between visits at baseline and at Month 18. The changes in SE over the 1.5-year follow-up period will be compared using ANOVA. The post hoc test will be carried out with Bonferroni correction to minimize the potential type I error due to multiple comparisons. The efficacy of myopic shift retardation of the therapeutic intervention is determined by dividing the difference in myopic shift between the treatment group and the control group with the myopic shift in the control group. The intention-to-treat analysis will be adopted to address the issue of loss to follow-up. The missing data in the repeated measures analysis will be dealt with generalized estimating equations (GEE). With one within-subject factor (time), one between-subject factor (treatment assignment) and their interactions, GEE will be employed to determine the treatment effect on the primary outcomes adjusted for some confounding factors, including age, gender, baseline SE, number of myopic parents, time spent on near works and outdoor activities.

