The secondary outcomes include the proportion of incident myopia, the proportion of fast myopic shift of SE, and the changes in mean axial length over the 1.5-year follow-up period. The analyses on the secondary outcomes will also be conducted with intent-to-treat principles. Using exact unconditional methods based on the Farrington-Manning score statistic, we will calculate the difference in the cumulative incidence of myopia among groups of different treatment assignment. As a binary outcome, the proportion of fast myopic shift of SE will be analyzed with Pearson’s chi-square test to compare the difference among groups. In addition, time-dependent Cox regression will be adopted to control the time-varying covariate in the analysis of the incidence of myopia and fast myopic shift of SE. Just like the analysis of myopic shift of SE, we will use ANOVA and Bonferroni correction to compare the mean change of axial length in each group. GEE will also be adapted to the treatment effect on this secondary outcome with the adjustment of the abovementioned confounding factors.

The exploratory outcomes include time to myopia onset, the changes in mean subfoveal choroidal thickness and amounts of near work/outdoor activities over the study period. In the analysis of time to myopia onset, we will assess survival analysis using a Kaplan–Meier method, with the significance based on the log-rank test. As a continuous variable, subfoveal choroidal thickness will be assessed with GEE to compare the changes among the three groups. The differences in the questionnaire items among the three groups will be estimated with ANOVA test.

The interval between the baseline visit and the last follow-up visit before school entrance is defined as “preschool stage”. The interval between the last follow-up visit before school entrance and the final visit is defined as “elementary school stage”. It is estimated that there will be nine months in both stages. The changes in SE and axial length in each stage are calculated as the difference in SE and axial length between the first and the last visits in the stage. We will use a paired t-test to compare the differences in mean change of SE and axial length between preschool and elementary school stages in each group.

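### The study eye is chosen on the same baseline SE reading from which change is measured, so within-arm SE shift is understated and the SE stage comparison leans towards faster shift after school entry

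*Protocol article*

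**What the plan says.** All references are to the Protocol article.

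- **Choice of eye.** Definition of outcome: "only the eye with less SE at baseline (less positive or more negative refractive error) in each child was included to analyze study outcomes". The rule applies to the analyses of both SE and axial length. Statistical analysis repeats the lower-SE rule but gives no time point.
- **Origin of change.** Primary outcome: "the change in mean cycloplegic SE between the baseline visit and subsequent 3-month visits over the study period in each group". Statistical analysis: "the 1.5-year myopic shift of SE is calculated as the difference in SE between visits at baseline and at Month 18".
- **Readings available.** Eye examinations: "At baseline visit and subsequent 3-month follow-up visits over the study period, all participants will receive the eye examination", including refraction before and after cycloplegia. Children are identified earlier, by the cycloplegic refraction of the kindergarten programme (YMVIP; Participants' recruitment and eligibility). No repeat baseline reading, two-eye average or correction is described.
- **Stages.** Statistical analysis: "The interval between the baseline visit and the last follow-up visit before school entrance is defined as" the preschool stage. The elementary school stage runs from that last visit to the final one, and "It is estimated that there will be nine months in both stages".
- **Stage test.** "We will use a paired t-test to compare the differences in mean change of SE and axial length between preschool and elementary school stages", separately in each group.
- **Percentage efficacy.** It is obtained by "dividing the difference in myopic shift between the treatment group and the control group with the myopic shift in the control group".

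**The concern.** Picking the lower of two readings picks partly on true refraction and partly on that day's error. The error part is negative on average in the chosen eye and is not repeated at Month 3 or later. This is regression to the mean, and it makes the chosen eye appear to move in the hyperopic direction after baseline in every arm.

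Three quantities have no protection from randomisation:

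- **Within-arm mean change**, which is how the primary outcome is worded.
- **The SE stage comparison.** Baseline enters only the preschool stage, so the expected stage difference is not zero when the true shifts are equal. The Discussion lists the comparison before and after school entry among the aims, and the Introduction presumes less pressure at preschool. The artefact points the way the authors expect, and does so in all three arms, so agreement between arms would not expose it.
- **Percentage efficacy**, whose denominator is the control-arm shift. The proportions with a fast myopic shift, also built on change from baseline, are lowered as well.

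**Working it through.** The plan states no figure for this effect, so there is none to reproduce.

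**Inputs from the Sample size calculation section:** 58 evaluable children per arm; SD of SE change 0.6 D; 1-year changes of -0.17 D (DIMS), -0.38 D (atropine) and -0.55 D (control); two-sided 0.05.

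**Assumed, because the documents give no value:** between-visit error SD per eye *s* = 0.10-0.20 D, independent between eyes; SD of the true between-eye difference *t* = 0.2-0.4 D. The minimum of three consecutive readings at a visit comes from one session, so averaging them does not remove between-visit error.

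**1. Offset in the chosen eye's baseline SE**

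b = s² × √(2/π) / √(t² + 2s²)

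Example, s = 0.15 and t = 0.3: 0.0225 × 0.798 / √(0.09 + 0.045) = 0.01795 / 0.3674 = 0.049 D.

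**2. Rejection rate of the SE stage test when the true stage shifts are equal**

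The test variable is (Month 9 - baseline) - (Month 18 - Month 9), with mean b. Let S be the observed SD of a nine-month change and ρ the correlation of true change between stages. Then

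variance = 2(S² - 2s²)(1 - ρ) + 6s²

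Scaling 0.6 D to nine months gives S between 0.6 × 0.75 = 0.45 and 0.6 × √0.75 = 0.52. I took ρ from 0 to 0.5.

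Example, s = 0.15, t = 0.3, S = 0.45, ρ = 0.5: variance = 0.1575 + 0.135 = 0.2925, SD 0.541. The noncentrality is 0.0489 / (0.541/√58) = 0.69. The noncentral t with 57 df rejects in 10.4% of trials, and only 0.4% are in the direction of slower shift after school entry.

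| s (D) | b over t = 0.4 to 0.2 (D) | Rejection, noncentral t | Range quoted |
|---|---|---|---|
| 0.10 | 0.019-0.033 | 5.4-7.9% | 5-8% |
| 0.15 | 0.040-0.062 | 6.7-13.7% | 7-15% |
| 0.20 | 0.065-0.092 | 9.5-20.9% | 10-22% |

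The quoted ranges are slightly wider at the top, to cover recalculation with comparable variance settings.

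**3. Percentage efficacy at 18 months**, scaling the 1-year figures by 1.5 (linearity is an assumption). Control 0.55 × 1.5 = 0.825 D; atropine 0.38 × 1.5 = 0.570 D; difference 0.255 D, which the offset leaves unchanged.

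- No offset: 0.255/0.825 = 30.9%
- b = 0.02: 0.255/0.805 = 31.7%
- b = 0.06: 0.255/0.765 = 33.3%
- b = 0.09: 0.255/0.735 = 34.7%

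**4. Does removing the link remove the effect?** With s = 0.2 and t = 0.3, simulated rejection returns to 4.9% for a pre-specified eye, for the two-eye mean, and for an eye chosen on a separate earlier reading. With the eligibility cut-offs also simulated, the screening rule leaves an offset of only 0.00-0.01 D.

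**The case against.** The best case for leaving the plan alone has four parts.

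- **The main inference is untouched.** The offset is equal across randomised arms in expectation, so the ANOVA, the Bonferroni comparisons and the GEE treatment contrasts of SE change are unbiased. This stands. A reader might infer that the randomised SE comparison is compromised; the documents do not support that.
- **The size is assumed.** This also stands. At s = 0.10 D the inflation is slight, and error shared by both eyes does not influence which eye is chosen. A reader might infer that the stage test rejects at twice the nominal rate or more once the error SD reaches 0.15 D. With variance matched to the planned 0.6 D that is not generally so: the range there begins at about 7%.
- **The stage test is ancillary.** It is not among the listed primary, secondary or exploratory outcomes, and it has no randomised contrast. But it serves an aim named in the Discussion, and the offset has a fixed direction.
- **The efficacy effect is small.** With SD 0.6 D and 58 per arm, the 95% half-width of an arm difference is 1.96 × 0.6 × √(2/58) = 0.22 D, beside which a few percentage points are minor. A reader might subtract 0.06 D from the 1-year control figure and get 0.17/0.49 = 35%. The plan's shift is over 18 months, where the same offset gives 33%.

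It could also be argued that baseline means the screening refraction. If so, the problem disappears, but the text uses the same word for the visit at which change begins and does not separate the two. Avoiding binocular interaction bias is a sound reason to analyse one value per child. It does not require choosing the eye on the baseline reading.

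**Conclusion.** The point holds as a limited one. Its direction follows from the text for any measurement error that is independent between eyes; its size rests on assumed error and between-eye SDs. For an error SD of 0.10-0.20 D, within-arm myopic SE shift from baseline is understated by about 0.02-0.09 D. The SE stage test rejects in roughly 5-22% of trials with no true stage difference, leaning towards faster shift after school entry. Percentage efficacy is slightly overstated.

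It does not extend to between-arm differences in SE change. Because the stage test is planned for both SE and axial length, a reader might assume that both are affected. The eye is not selected on axial length, so that test is largely unaffected. This is worth correcting because the change is cheap, not because the trial's main comparison is at risk.

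**What to change.** In Definition of outcome and in Statistical analysis, state one rule that does not depend on the baseline-visit SE. Either analyse SE change on the mean of both eyes, or fix one eye in advance: the lower-SE eye at the YMVIP screening refraction, or the right eye. Keep that eye throughout and measure change from the separate baseline-visit reading. If screening and baseline are the same examination for some children, the screening option does not work for them, and the two-eye mean or the right eye should be used.

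The cost is wording only, with no new visits, data or participants. The screening option has a real drawback. The study eye will not be the lower-SE eye at the baseline visit in a share arccos[t²/(t² + 2s²)]/π of children. That is 15% at s = 0.10, t = 0.4 and 39% at s = 0.20, t = 0.2. The two-eye mean avoids choosing an eye at all.

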#### Adverse event

In the DIMS group, the main adverse event will likely be peripheral blurred vision, dizziness and eyestrain after wearing spectacles. The main adverse event in the 0.01% ATR group will likely be photophobia, blur near vision, and allergic conjunctivitis. Study staff will record any adverse event during the study period and promptly address the subjects’ signs and symptoms.

#### Follow-up schedule

In addition to the baseline visit, all participants will be arranged to have follow-up visits at month 3, month 6, month 9, month 12, month 15, and month 18 after randomization (Fig 1). The subjects in the treatment groups will have additional visits for tolerance assessment in week 2. Most participants will enter elementary school after the first nine months of the follow-up period. The differences in variables of interest between the baseline and each follow-up visit will be analyzed.

### Eye examinations

At baseline visit and subsequent 3-month follow-up visits over the study period, all participants will receive the eye examination, including assessments of uncorrected/corrected visual acuity, external eye, ocular alignment, extraocular muscle motility, axial length measurement, choroidal thickness measurement, refractive status before and after cycloplegia, and a dilated fundus examination.

#### Assessment of non-cycloplegic autorefraction, visual acuity, and stereopsis

The refractive status will be first measured with a table-mound autorefractor (Topcon KR-1, Tokyo, Japan). At least three autorefraction readings will be acquired and averaged. The study staff will assess uncorrected visual acuity monocularly using a Snellen eye chart at six meters. When the right eye is tested, the left eye is covered using an eye occluder and vice versa. If the children already have the DIMS spectacles at follow-up visits, visual acuity will be assessed again when they wear their spectacles. Binocular stereopsis assessment will be carried out by study staff using NTU random-dot stereogram.

#### Assessment of ocular alignment, extraocular muscle motility and intraocular pressure

Ocular alignment will be assessed with cover and uncover test. Eye movement and ocular stability will be evaluated as well. Intraocular pressure will be measured with non-contact tonometry.

#### Assessment of external eye and anterior segment

The conjunctiva, cornea, anterior chamber, pupil size, iris, lens and anterior vitreous will be assessed using slit-lamp biomicroscopy. Children with acute keratoconjunctivitis will not be allowed to receive cycloplegic refraction, ocular biometry, or fundus examination.

#### Pupil dilation and cycloplegic autorefraction

Three drops of 1% tropicamide (administered five minutes apart) will be instilled to induce cycloplegia. Cycloplegia is presumed complete when the penlight cannot constrict the pupil anymore. If the pupil still responds to penlight stimulation, one more cycloplegic eyedrop and an additional 10-minute wait will be required before performing cycloplegic autorefraction with a table-mound autorefractor (Topcon KR-1, Tokyo, Japan). The refractive error will be assessed with at least three consecutive autorefraction readings from each participant.

#### Ocular biometry measurement

Axial length and other anatomical measurements of the eye, such as keratometry and anterior chamber depth will be carried out with an optical biometer (Lenstar LS 900, Haag-Streit, Verkauf, Switzerland).

#### Choroidal thickness measurement

Subfoveal choroidal thickness will be measured with optical coherent tomography (AgnioVue; Optovue, Fremont, CA, USA).

#### Dilated fundus examination

After pupil dilation, vitreous body, optic nerve head and posterior pole will be examined with binocular indirect ophthalmoscope.

### Questionnaire survey and compliance assessment

To collect information on potential myopia-related risk factors, the parent-administered questionnaire and eye examinations for all participants at baseline and 9- and 18-month follow-up visits will be conducted. This questionnaire comprises four sections and 16 questions regarding demographic data, parental myopia, medical information, and out-of-school behaviors such as time spent on near work, outdoor activities, sleeping and after-school care service or tutorial programs. These questions are closed-ended and have responses of yes/no options or a list of ordered choices. The respondents were asked to check the choice they felt was the most proper. Table 1 summarizes the survey questions in the questionnaire.

**Table 1 pone.0312935.t001:** Survey questions and responses in the questionnaire.

Caregiver’s information
• Your relationship with the child: □mother, □father, □paternal grandparent, □maternal grandparent, □others______ • Age • Gender • Occupation
• Education level: ➢Child’s father: □primary school, □junior high school, □senior high school/vocational school, □junior college or university, □graduate school or above ➢Child’s mother: □primary school, □junior high school, □senior high school/vocational school, □junior college or university, □graduate school or above • Do the parents have myopia? □no_ none has myopia, □yes_ only father has myopia, □yes_ only mother has myopia, □yes_ both have myopia
**Medical history of the child**
• Does your child have past ocular history? □no, □yes ➢If yes, what is the disease? □congenital glaucoma, □congenital cataract, □retinopathy of premature, □strabismus, □asthma, □ocular trauma, □ocular surgery, □others______
• Did you have your child’s eyes examined by an ophthalmologist over the past year? □no, □yes
• Has your child received any ophthalmic treatment over the past year? □no, □yes ➢If yes, what kind of the treatment? □cycloplegic agents, □spectacles, □orthokeratology, □patching for amblyopia
**Lifestyle, near-work habits and outdoor activity of the child**
• In recent one week, how much time a day did your child spend on doing homework (such as reading, writing, drawing and playing musical instruments)? ➢On weekdays: □none, □< 30 minutes, □≥ 30 minutes but < 1 hour, □≥ 1 but < 2 hours, □≥ 2 but< 4 hours, □≥ 4 hours ➢On weekends: □none, □< 30 minutes, □≥ 30 minutes but < 1 hour, □≥ 1 but < 2 hours, □≥ 2 but< 4 hours, □≥ 4 hours
• In recent one week, how much time a day did your child spend on using screen-based devices (such as watching television and playing smartphones, computers, tablets or video games)? ➢On weekdays: □none, □< 30 minutes, □≥ 30 minutes but < 1 hour, □≥ 1 but < 2 hours, □≥ 2 but< 4 hours, □≥ 4 hours ➢On weekends: □none, □< 30 minutes, □≥ 30 minutes but < 1 hour, □≥ 1 but < 2 hours, □≥ 2 but< 4 hours, □≥ 4 hours • In recent one week, how much time a day did your child spend on after-school outdoor activities (such as playing balls, swimming or cycling)? ➢On weekdays: □none, □< 30 minutes, □≥ 30 minutes but < 1 hour, □≥ 1 but < 2 hours, □≥ 2 but< 4 hours, □≥ 4 hours On weekends: □none, □< 30 minutes, □≥ 30 minutes but < 1 hour, □≥ 1 but < 2 hours, □≥ 2 but< 4 hours, □≥ 4 hours • In recent one week, how long did your child sleep every night? □<7 hours, □≥ 7 but <8 hours, □≥ 8 but <9 hours, □≥ 9 but <10 hours, □≥10 hours
**Attendance of after-school activity (after entering elementary school)**
• Does your child attend after-school activity after entering elementary school? □yes, □no, □not sure ➢If yes, what kind of after-school activity? □on-campus care service/club activity, □off-campus care service, □off-campus tutoring program/cram school, □off-campus compound (care and tutoring) program ➢If yes, how much time a week dose your child spend on after-school activity? □< 5 hours, □≥ 5 hours but < 10 hours, □≥ 10 hours ➢If yes, how many days a week does your child attend on after-school activity? □1 day, □2 days, □3 days, □4 days, □5 days, □6 days, □7 days ➢If yes, how long has your child attended after-school activity? □< 1 semester, □≥ 1 but < 2 semesters, □≥ 2 but < 3 semesters, □≥ 3 semesters

An unpublished study has been conducted among 40 six- to seven-year-old children (22 males and 18 females) and their parents to evaluate the concurrent validity (the agreement between children and parents) and test-retest reliability (parents’ reproducibility estimates) of the questionnaire survey described above. For lifestyle, near work, outdoor activity, attendance of after-school care/tutoring activity, the five-day test-retest reliability was examined using McNemar’s tests (all P > 0.05), and the measure agreement between children and their parents was examined using Cohen’s kappa coefficient (0.68–0.81), which provide the evidence of adequate reliability and validity of this questionnaire.

In addition to the questionnaire, we will give each participant’s parents or caregivers a diary booklet and urge them to record school attendance during the school day and amount of after-school near work activity and outdoor activity. In the treatment groups, atropine eyedrop use or DIMS spectacles wear will also be recorded in the diary daily. Treatment compliance and adherence level will be assessed based on the number of days with atropine use/DIMS spectacles worn as recorded in the dairy. Participants will be considered to have good treatment compliance if the number of days with treatment adherence is more than 80% of the total days that the participants stay in this trial.

